### Trial design {8}

This is a multicentre randomised clinical trial consisting of two parallel groups with equal randomisation to detect the superiority of one intervention over the other. Randomisation of the participants to one or two groups will be undertaken to ensure unrestricted equal participant allocation (1:1). This process will be undertaken centrally to ensure random allocation and concealment.

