### Interventions

#### Explanation for the choice of comparators {6b}

Early diagnosis and appropriate management are recommended for the unerupted maxillary incisor teeth. Following the removal of a supernumerary tooth, the retrospective evaluation suggests that between 49 and 91% of permanent maxillary incisors will erupt spontaneously [11–14]. Although these figures appear to be favourable, there is a large variation in the reported time taken for the incisor to erupt, which can be up to 18 months [12]. Eruption of the maxillary incisor can be facilitated by space creation in conjunction with the removal of the obstruction [7, 12, 14–18]. However, between 30 and 54% of the impacted incisors still require further surgical intervention [11, 13, 14, 19] and some form of orthodontic alignment [16]. In addition to the surgical removal of any obstruction, surgical exposure of the unerupted maxillary incisor may also be undertaken. In these circumstances, early orthodontic traction can enhance facilitated eruption [20]. Based on retrospective studies, the success of surgical exposure combined with orthodontic traction has been reported to exceed 90% [21]. However, the type of surgical exposure procedure undertaken in conjunction with orthodontic traction may affect both long-term gingival and periodontal outcomes of the erupted incisor [22].

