#### Criteria for discontinuing or modifying allocated interventions {11b}

In either group 1 or group 2, if after 6 months following removal of the supernumerary tooth the central incisor has failed to erupt, records (intra-oral photographs, study models and radiographs) will be taken. Following these records, a clinical decision will be made to either continue monitoring the eruption of the incisor, arrange a further surgical intervention or apply piggyback orthodontic mechanics (0.014-in. nickel titanium or elastomerics and 0.018-in. stainless steel archwires) to erupt the tooth.

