#### Sample size {14}

Sample size calculation was based on three previous studies [11, 12, 14], random-effects meta-analysis of which indicated that in 58% of cases (95% = 40–75%; *I*^2^ = 85%), the maxillary permanent central incisor erupts spontaneously after surgical removal of the supernumerary tooth. Assuming a moderate relative risk = 1.50 as clinically relevant, equal 1-1 distribution between the groups and aiming to find a difference using a chi-square test with *α* = 5% and *β* = 20% (power of 80%), a total of 40 patients per group would be needed. Adding an additional 15% for possible drop-outs, the aim was set at 46 patients/per group (92 in total).

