## Statistical methods

### Statistical methods for primary and secondary outcomes {20a}

The primary outcome of the trial is the successful eruption (yes/no) of the impacted maxillary incisor, which is ascertained clinically in an objective matter and is clinically relevant (binary outcome). Secondary outcomes planned include (i) time taken for the maxillary incisor to erupt clinically after surgical removal of the supernumerary (continuous outcome in days), (ii) gingival aesthetics outcome according to Parkin et al. [26] (continuous outcome on a 100-cm visual analogue scale [VAS]) and (iii) patient-related outcomes included in the Oral Health-Related Quality of Life Questionnaire [24] (continuous scale outcome with total score and sub-scores for each category). Possible risk factors that are planned a priori to be investigated include patient age, patient sex, patient ethnicity, impacted incisor’s maturity, impacted incisor’s position (height, inclination and orientation; as described in the trial’s protocol) and the supernumeraries’ number or morphology (conical, premolariform, incisiform, complex odontoma, etc.). The initial crude differences between the groups will be assessed with the chi-square test for the primary outcome or the t-test for independent samples for the secondary outcomes (or non-parametric equivalents). The crude effect of intervention groups on the primary/secondary outcomes (with patient as the unit of analysis) will be further assessed with generalised linear models (after appropriate model diagnostics) with relative risk (RR) for the primary outcome or unstandardised regression coefficient for the secondary outcomes and their corresponding 95% confidence interval (CI). Furthermore, regression models will be adjusted for the potential impact of any of the above-listed confounders, by adding one covariate at a time in the simple model and retained if the change-in-estimate is at least 10% [27]. All analyses will be done per protocol by the statistician in a blind manner using a coded dataset in Stata 14.2 (StataCorp., College Station, TX, USA) with a significance level set at a two-sided P-value of 0.05 for all analyses.

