### Methods for additional analyses (e.g. subgroup analyses) {20b}

Except for the adjusted-for-confounders analyses detailed above, no other additional analyses or subgroup analyses are planned.

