### Methods in analysis to handle protocol non-adherence and any statistical methods to handle missing data {20c}

Statistically significant RRs will be translated in a clinically relevant manner using risk differences and the number needed to treat. If multiple impacted teeth per patients are included, within-patient clustering will be taken into account with robust standard errors. If any centre effects are identified, these will be accounted for with a random term in the model.

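### All analyses of this unblinded superiority trial are fixed as per protocol, and no analysis by allocated arm is planned beside them

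*Protocol article*

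**What the plan says.** Under Trial design {8}, the protocol article describes "two parallel groups with equal randomisation to detect the superiority of one intervention over the other". Section {17a} says that neither clinicians nor participants can be blinded; the statistician and the assessor of the baseline radiographs are.

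The analysis population is set in one sentence of {20a}: "All analyses will be done per protocol by the statistician in a blind manner using a coded dataset". The article neither defines a per-protocol set nor mentions analysis by allocated arm. Section {20b} says that, apart from the confounder-adjusted models, "no other additional analyses or subgroup analyses are planned". Section {20c}, whose heading covers non-adherence and missing data, opens with "Statistically significant RRs will be translated in a clinically relevant manner using risk differences and the number needed to treat" and goes on to clustering and centre effects.

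For a tooth still unerupted at 6 months in either group, {11b} says "a clinical decision will be made to either continue monitoring the eruption of the incisor, arrange a further surgical intervention or apply piggyback orthodontic mechanics".

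**The concern.** In a superiority trial, the comparison that randomisation protects is the one between the arms as allocated. A per-protocol analysis removes children according to what happened after randomisation. If those events are related to eruption, the arms no longer differ by chance and treatment alone.

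Here such a link is easy to imagine. In group 1, a child whose chain was not bonded, or who stopped traction, may also be a child whose tooth did not come through. In group 2, a child given traction before 6 months may have a slow tooth. Removing the first kind flatters traction; removing the second flatters monitoring. The direction of any bias therefore cannot be known in advance.

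The choice covers every analysis, so the published result would have no as-randomised figure against which to check it. The trial is meant to inform treatment guidelines, which makes that gap matter.

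**Working it through.** **1. Inputs from the plan (Sample size {14}).** Eruption 58% after removal of the supernumerary alone; target relative risk 1.50, so 0.58 × 1.50 = 0.87 with traction; two-sided α 5%; power 80%; 40 per group, raised to 46.

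**2. The plan's own figure.** For 58% against 87%, the two-proportion formula gives 37 per group without continuity correction and 43 with it; the Fisher exact test gives 41. The stated 40 lies within that range, and 40 × 1.15 = 46. The sample size is not in dispute here.

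**3. Primary outcome with no true effect (assumed exclusions).** Let both arms erupt at 58%, and let a fraction f of group 1 be dropped, of whom a proportion e erupted. The eruption rate among those kept is

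p = (0.58 − f·e) / (1 − f), and the apparent RR is p / 0.58.

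The type I error uses the pooled normal test with n₁ = 46(1 − f) and n₂ = 46.

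| f (children of 46) | e = 0, all failures: p, RR, error | e = 0.29: RR, error | e = 0.58, unrelated to outcome: RR, error |
|---|---|---|---|
| 5% (2.3) | 0.611, 1.05, 6.0% | 1.03, 5.2% | 1.00, 5.0% |
| 10% (4.6) | 0.644, 1.11, 9.4% | 1.06, 6.1% | 1.00, 5.0% |
| 15% (6.9) | 0.682, 1.18, 16.1% | 1.09, 7.6% | 1.00, 5.0% |

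Worked row, f = 10%, e = 0:
- p = 0.58/0.90 = 0.644, n₁ = 41.4, difference 0.064.
- Pooled rate (41.4 × 0.644 + 46 × 0.58)/87.4 = 0.611; null standard error √[0.611 × 0.389 × (1/41.4 + 1/46)] = 0.1045.
- Standard error under the distorted rates √[0.644 × 0.356/41.4 + 0.58 × 0.42/46] = 0.1041.
- Error = Φ[(0.0644 − 1.96 × 0.1045)/0.1041] + Φ[(−0.0644 − 1.96 × 0.1045)/0.1041] = 0.089 + 0.005 = 0.094.

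If the failures are dropped from group 2 instead, the apparent RR is 0.58 ÷ [0.58/(1 − f)] = 1 − f, that is 0.95, 0.90 or 0.85. If both arms lose the same fraction of failures, the RR stays at 1.

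**4. What analysis as randomised costs.** Suppose a fraction f of group 1 receives no traction and erupts at 58%. The group 1 rate is 0.87(1 − f) + 0.58f.

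| f | Group 1 rate | RR | Power, 46 per group | Power, 40 per group |
|---|---|---|---|---|
| 0% | 0.870 | 1.50 | 89% | 84% |
| 5% | 0.856 | 1.475 | 85% | 79% |
| 10% | 0.841 | 1.45 | 80% | 74% |
| 15% | 0.826 | 1.425 | 74% | 68% |

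**5. Children unerupted at 6 months.** On planning rates, 1 − 0.58 = 42% of group 2 and 1 − 0.87 = 13% of group 1: about 46 × 0.42 = 19 and 46 × 0.13 = 6 children. The 95% interval in {14} (40–75%) gives 25–60% for group 2. The 58% is the pooled share in which "the maxillary permanent central incisor erupts spontaneously after surgical removal of the supernumerary tooth", and no 6-month limit is stated for it.

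**The case against.** **The phrase may be loose.** It stands in a sentence about how the work is done (blinded statistician, coded dataset, named software), and no exclusion rule follows it. It could mean only that the protocol will be followed. That is possible, but in a statistical methods section the technical meaning is the natural one, and no other sentence supplies an as-randomised analysis. If the loose meaning was intended, the correction is the same.

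**The article is condensed.** A definition of the analysis set may sit in the full protocol or the analysis plan, and the thin text under {20c} is no finding in itself. The point here rests on what {20a} states for all analyses; a later document specifying analysis as randomised would contradict it.

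**Exposure may be small.** Randomisation follows space creation ({11a}), so losses in that phase come before allocation, and the arms then part at a single operation. The coded dataset also limits any choice of exclusions at the analysis stage. Both points stand as reasons for expecting few exclusions. Neither makes the exclusions that do occur independent of outcome, because unblinded sites deliver the treatment and record it.

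**A stronger reading is tempting.** A reader might infer that children unerupted at 6 months will be removed from the later outcomes (alignment time, gingival aesthetics, quality of life), mostly from group 2, and that this would bias those results heavily. The documents do not support that. Section {11b} prescribes the 6-month decision for both groups, one of its options is simply to go on monitoring, and a group 2 child observed for 6 months has completed the allocated period. Such a child has followed the protocol. The decision also comes after the primary endpoint and cannot change it.

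**Conclusion.** The point holds in a limited form. The plan fixes per protocol as the only analysis population of an unblinded superiority trial. Under the usual meaning, that allows exclusions after randomisation from the primary comparison, with no as-randomised result beside it. It should be changed.

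The size is an illustration of vulnerability, not a forecast. Losing 5–15% of one arm, roughly two to seven children, takes the type I error from 5% to about 6–16% if all were failures, to about 5–8% if they erupted at half the usual rate, and leaves it at 5% if exclusion is unrelated to eruption. The excluded fractions and their eruption rates are assumptions.

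For the later outcomes, only a brief conditional remark is warranted. The 42% of group 2 and 13% of group 1 expected to be unerupted at 6 months should not count as deviators, and the plan would do well to say that they stay in.

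**What to change.** In {20a}, replace the per-protocol statement with:

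*All randomised children with outcome data are analysed in the arm to which they were allocated, whatever treatment they received; any option taken under {11b} is part of the allocated strategy and is no reason for exclusion.*

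A per-protocol analysis may be kept as supplementary, with its exclusions defined in advance; {20b} then needs a clause to allow it.

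The change needs no extra visits or measurements and leaves the sample size as it is. It has two costs. Non-adherence dilutes the estimate somewhat (RR 1.45 instead of 1.50 if 10% of group 1 go without traction, with power about 80% at 46 per group and 74% at 40). The late outcomes will compare strategies, immediate traction against 6 months of monitoring followed by a clinical decision, and not traction against purely spontaneous eruption.

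The wording does not settle how a tooth that never erupts enters the time-to-eruption analysis. That is a separate censoring question under any analysis population.

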### Interim analyses {21b}

Stopping of the trial could also be based on interim data analysis if, clearly, one treatment is better than the other, but no interim analysis is planned.

### Methods for additional analyses (e.g. subgroup analyses) {20b}

Except for the adjusted-for-confounders analyses detailed above, no other additional analyses or subgroup analyses are planned.

### Methods in analysis to handle protocol non-adherence and any statistical methods to handle missing data {20c}

Statistically significant RRs will be translated in a clinically relevant manner using risk differences and the number needed to treat. If multiple impacted teeth per patients are included, within-patient clustering will be taken into account with robust standard errors. If any centre effects are identified, these will be accounted for with a random term in the model.

### Plans to give access to the full protocol, participant-level data and statistical code {31c}

The protocol will be published on a publicly accessible database, ISRCTN Registry (https://www.isrctn.com/). The full anonymised dataset of the trial will be made openly available through Zenodo.

### Oversight and monitoring

#### Composition of the coordinating centre and trial steering committee {5d}

A monitoring/steering/safety committee will not be set up for this study. The team at the Kings Clinical Trials Unit will be responsible for the randomisation of participants to the trial arms. Each primary investigator and their dental care team at each recruitment site will be responsible for local organisation of the trial including identifying potential recruits and taking informed consent and data collection. The trial will be supervised by the chief investigator who will organise meetings every 4–6 months with the primary investigators at each recruitment site to discuss the progress of the trial and any operational or clinical challenges that have be encountered. A stakeholder and public involvement group (SPIG) was used to support the justification of the trial during the ethical approval process. However, a SPIG will not be required during the conduct of the trial.

#### Composition of the data monitoring committee, its role and reporting structure {21a}

A monitoring/steering/safety committee will not be set up for this study. The chief investigator will be responsible for the ongoing management of the study. A data monitoring committee is not required as this is a low-risk intervention (comparison of existing standards of care), and the ethics committee did not request a data monitoring committee.

#### Adverse event reporting and harms {22}

No serious adverse events (SAEs) are expected to occur as part of this trial. Participants enrolled in the trial will be undergoing routine orthodontic treatment within the orthodontic departments of each recruitment site, and this treatment does not differ from any other patients that are treated in the respective departments. Subject safety will be assessed for all patients undergoing treatment within the department (physical examination, adverse event reporting). Where an SAE is related to the study procedures or is an unexpected occurrence, then it will be reported immediately upon knowledge of the event to Guy’s and St Thomas’ R&D within 24 h. For all other AEs, these will be reported to R&D when copied into the Annual Progress Report. The principal investigators at all sites must report all SAEs to the chief investigator first where possible. The chief investigator is then responsible for reporting events to R&D.

#### Frequency and plans for auditing trial conduct {23}

The sponsor will monitor and conduct audits on a selection of studies in its clinical research portfolio. Monitoring and auditing will be conducted in accordance with the UK Policy Framework for Health and Social Care 2017 and in accordance with the sponsor’s monitoring and audit procedures. This study may be identified for audit by any of the following indications: project may be identified via the risk assessment process, an individual investigator or department may request an audit, a project may be identified via an allegation of research misconduct or fraud or a suspected breach of regulations, projects may be selected at random as per the Department of Health which recommends that trusts should be auditing a minimum of 10% of all research projects and projects may be randomly selected for audit by an external organisation and internal audits conducted by a sponsor’s representative.

#### Plans for communicating important protocol amendments to relevant parties (e.g. trial participants, ethical committees) {25}

If required, any protocol amendments will be communicated to local R+D departments and subsequent ethics committees. Following this, a revised protocol would be sent to the PI at all recruitment sites. The clinical trial register will also be updated.

#### Dissemination plans {31a}

The chief investigator, PhD student or treating dental care team (research team) at each recruitment site will inform the patients about the study findings after the trial ends. A summary sheet regarding the results of the study will be provided. The reporting of this trial will be in accordance with the CONSORT guidelines [28]. The results of the study will be disseminated via appropriate scientific publications (peer-reviewed journals) and presentations at conferences/meetings. Additionally, a printed copy of the accepted scientific publication following completion of the study will be posted to each participant (optional). The use of professional writers will not be employed.

## Discussion

This trial was planned to commence prior to 2020. However, given the disruption caused to clinical services by the COVID-19 pandemic, a delay in commencing would appear advantageous, but challenges still remain. The recruitment of participants into this trial is currently limited to secondary care services (orthodontics, paediatrics and oral survey) which are under pressure to reduce patient treatment waiting lists and restoring clinical activity to pre-COVID levels. The participants with the index condition for this trial are deemed a high need for treatment as per the Index of Orthodontic Treatment Need (IOTN) [27] and are commonly referred from primary care to second care environments as a multi-disciplinary management is often required. On this basis, we do not anticipate difficulty in achieving the required sample size as recruitment of patients is being undertaken across nine sites. However, future rises in COVID-19 infections could impact recruitment especially if national restrictions are reactivated and staff at recruitment sites are redeployed. To manage potential recruitment issues, the inclusion of additional recruitment sites will be considered.

As encountered by other clinical trials in orthodontics, blinding of both participants and investigators at recruitment sites will not be possible. To minimise bias, the randomisation (allocation and concealment) will be undertaken centrally at a Clinical Trials Unit. Furthermore, both the investigator assessing the clinical records and the statistician will be unaware of the participant trial arm allocation.

### Trial status

Protocol version 1 (01/11/2021). Recruitment is anticipated to begin on 1 July 2022 and end 6 months before the end of the trial (01/11/2024).

## Data Availability

Members of the direct care team will have access to the personal data. This also includes a PhD student who is part of the direct care team. Regulatory authorities and NHS R&D offices at each recruitment site will monitor and conduct audits on a selection of studies in its clinical research portfolio.
